## Abstract

**Background:**

Stuttering is a condition that usually begins in childhood and may continue into adulthood. In this study, it is suggested that the combined approach of transcranial direct current stimulation (tDCS) with fluency shaping techniques will result in greater improvements in speech fluency compared to using fluency shaping techniques alone.

**Methods:**

This study is designed as a randomized, double-blind, sham-controlled clinical trial. All participants will participate in speech therapy sessions. The intervention group will receive anodal transcranial direct current stimulation, while the control group will experience sham stimulation. Participants will be randomly assigned to one of these groups. Before starting the treatment program, a preintervention assessment will be conducted to determine the severity of stuttering. Once these assessments are completed, each participant will take part in intervention sessions. Post-intervention evaluations will take place immediately after and six weeks after the final intervention session. Additionally, to evaluate the long-term stability of the treatment results, follow-up evaluations will be carried out three months post-treatment. The primary outcome measure—the ratio of stuttered syllables—will be evaluated during pre-, post-, and follow-up assessments; secondary outcomes will encompass scores from the Overall Assessment of the Speaker's Experience of Stuttering, severity ratings, and evaluations of speech naturalness.

**Conclusions:**

The results of this study will provide evidence regarding the effectiveness of combining tDCS with fluency shaping intervention on stuttering. This effect is likely to involve not only a reduction in SS% but also improvements in the overall quality of life for adults who stutter.

**Trial registration:**

IRCT20230907059369N1.

## Introduction

1

Stuttering is a neurodevelopmental disorder that affects speech fluency. It is characterized by interruptions in the natural rhythm and flow of speech production [1]. It involves involuntary repetitions and prolongations of speech sounds and syllables, and temporary interruptions or blocks in the natural flow of speech. Although the natural recovery rate is high during the initial three years after the onset of stuttering, around 1 % of adults globally continue to experience chronic stuttering [2]. Stuttering can impact various aspects of an individual's life. People who stutter(PWS) report experiencing negative reactions from others, difficulties communicating in important situations, lower levels of life satisfaction, and reduced ability to achieve their life goals [3]. Stuttering is classified as a “multifactorial” disorder involving genetic factors and neurological anomalies. However, there is a consensus among researchers that it is neurological in nature [4].

Although multiple therapeutic approaches have been developed in conjunction with various theoretical paradigms regarding the nature and etiology of stuttering, behavioural stuttering treatments have demonstrated the highest level of evidence [[5], [6], [7]]. However, some previous treatments reported changes in neurological functions of people who stutter after behavioural treatments [[8], [9], [10], [11]]. In these treatments, the individual learns a new speech pattern that requires extensive practice and time for generalization to everyday situations. The implementation of this new pattern may sometimes affect the naturalness of the individual's speech, which consequently reduces acceptance of the new method [12]. Behavioral “fluency shaping” therapies, which aim to modify factors like speech tempo, prosody, rhythm, speech onsets, and breathing techniques, have proven effective in significantly reducing the severity of stuttering, achieving less than 1 % of stuttered syllables [10]. Fluency-shaping therapies have been shown to reduce over-activation observed in the right hemisphere, normalize activity patterns in the basal ganglia, and reactivate the left-hemispheric cortical regions [[9], [10], [11],^13^,^14^].

Enhanced fluency is furthermore accompanied by increased functional connectivity within the sensorimotor integration network. In particular, two specific connections display strengthening; the left inferior frontal gyrus shows enhanced connectivity with the precentral gyrus at the site of the left laryngeal motor cortex, and the left inferior frontal gyrus demonstrates heightened connectivity with the right superior temporal gyrus. Consequently, the neural remediation linked with therapy is based on a strengthened integration of the command-to-execution pathway in conjunction with an enhanced auditory-to-motor coupling [15,16]. Nevertheless, maintaining therapeutic gains requires ongoing practice and training, as sustained improvements in fluency remain challenging to achieve without continuous intervention, Therefore, the relateralization of the speech-related neural network is commonly only a temporary effect, and represents an ultimately inadequate repair process overall [10]. As a result, there is an ongoing need to explore and develop novel therapeutic approaches to more effectively improve or alleviate stuttering symptoms [4].

Recent research has proposed integrating neuromodulation techniques with traditional therapeutic interventions. Neuromodulation has demonstrated the capacity to enhance brain function through the application of NIBS techniques. Non-invasive brain stimulation provides a means for direct interaction with the mechanisms of neural tissue. Consequently, it has been used to gather further and ‘real-time’ understanding of the impaired or abnormal motor functions that characterize developmental stuttering. In general, NIBS techniques can effectively alter neural functioning patterns through modulation of brain network activity [4]. One of the non-invasive brain stimulation methods that has been designed and used for the treatment of brain disorders is transcranial direct current stimulation (tDCS) [17].

In tDCS, an electrical current is applied between two or more electrodes, which include a negatively charged cathode and a positively charged anode, strategically positioned on the scalp. The administration of this current (with an intensity of 1–2 mA) induces minor modifications to the resting membrane potential of cortical neurons located within the surrounding brain tissue [17]. Specifically, within the framework of established protocols, cathodal stimulation affects neuronal compartments by inducing hyperpolarization, which leads to a decrease in neuronal excitability. In contrast, anodal stimulation causes depolarization, resulting in an overall increase in excitability at the macroscale level [[18], [19], [20], [21]].

Previous evidence indicates that the combination of non-invasive brain stimulation and behavioral interventions results in greater improvements [4]. Findings from these studies have prompted researchers to explore the utilization of tDCS as an adjunctive method in the treatment of speech fluency disorders in adults who stutter. The application of brain stimulation techniques for the treatment of stuttering in adults who stutter (AWS) is a novel approach, with comparatively limited research conducted thus far to other neurogenic communication disorders, such as aphasia or apraxia of speech. Recent investigations have shown that tDCS facilitates speech fluency in adults who stutter when combined with a fluency intervention [[22], [23], [24], [25], [26], [27]]. Recent findings indicate that abnormalities in the frontal cortex are present in individuals who stutter [28], identifying this region as a potential target for tDCS, which has been explored in recent studies [22,23,25]. Recently, a limited number of studies have explored the application of tDCS in conjunction with speech restructuring techniques that incorporate external timing cues (such as choral speech and metronome-timed speech) for the intervention of stuttering in AWS [[22], [23], [24], [25]].

This study further investigated the efficacy of tDCS for reducing observable and covert stuttering behaviors with more number of stimulation sessions and dosage, and while person who stutter control their fluency using the techniques that they have learned during the treatment. In previous studies, participants experienced fluent speech during brain stimulation with the external helps (e.g., unison speech, delayed auditory feedback (DAF), or metronome pacing) [[22], [23], [24], [25], [26]], However, in this study, participants be trained to developed self-control skills using fluency-shaping techniques during brain stimulation [29,30]. Additionally, tasks during brain stimulation in earlier studies were limited to reading sentences, passages, or monologues [[22], [23], [24], [25], [26], [27]], In contrast, in this study we stimulated the brain while the person performed various tasks such as reading, monologues, dialogues with the clician, dialogues with strangers, and telephone conversations with friends and strangers. This approach is based on findings suggesting that PWS encounter greater difficulties in maintaining fluent speech during cognitively demanding conversational tasks, as well as increased challenges in sustaining fluency when engaged in complex speech tasks that require syntactic or linguistic processing [[31], [32], [33]]. Also, AWS experience heightened difficulties in sustaining speech fluency during complex social interactions compared to private speech contexts, primarily due to increased anticipation and social pressures [34,35]. Furthermore, stimulation dosage in this study will be increased compared to previous studies, which typically used intensities of 1, 1.5, or 2 mA in 20-min sessions per day [[22], [23], [24], [25], [26], [27]]. This adjustment will be based on research suggesting that increased stimulation duration and intensity will not cause adverse effects, even in children, and will enhance the efficacy of treatment. Additionally, trends and suggestions in other areas of speech pathology will be explored [[36], [37], [38]].

The aim of this research will be to investigate the effects of adjunctive non-invasive brain stimulation on speech fluency in adults with stuttering. To accomplish this goal, two groups of adult participants who stutter will be recruited, namely a sham tDCS group and an anodal tDCS group. In the sham tDCS group, participants will receive sham stimulation simultaneously with the fluency shaping intervention, whereas those in the anodal tDCS group will undergo anodal tDCS in conjunction with the fluency intervention. It will be hypothesized that combining the fluency intervention with anodal tDCS aimed at the left IFG will produce more favorable outcomes than the sham tDCS control condition in improving speech fluency among adults who stutter.

## Methods

2

### Study design

2.1

This study is structured as a randomized, double-blind, sham-controlled clinical trial that will be performed to assess the efficacy of anodal tDCS in conjunction with a fluency shaping intervention focused on enhancing speech fluency in adults who stutter. Participants will be randomly assigned to either the control group or the intervention group. In the anodal tDCS group, participants will undergo fluency shaping intervention alongside anodal tDCS, while the sham tDCS group will receive sham tDCS concurrently with the fluency shaping intervention. The study will be conducted at the Speech Therapy Clinic and tDcs lab, School of Rehabilitation, Tehran University of Medical Sciences. The findings will be reported based on the CONSORT (Consolidated Standards of Reporting Trials) guidelines [39]. This trial has been registered at the Iranian Registry of Clinical Trials (IRCT code: IRCT20230907059369N1), where detailed information about the study protocol, inclusion and exclusion criteria, interventions, outcomes, and ethical approval can be found. The trial registration process was completed before the enrollment of the first participant. The current protocol is reported according to the Standard Protocol Items: Recommendations for Interventional Trials (SPIRIT) guideline [40].

Data will be gathered at four different time points: one week before the intervention, immediately after, 6 weeks after, and 3 months after the intervention. We will examine the effectiveness of anodal tDCS combined with fluency shaping techniques in improving speech fluency by comparing the outcomes of the different treatments. In pre-treatment assessments, we will measure primary and secondary outcome measures before treatment. Pre-treatment assessments will be conducted to evaluate the severity of stuttering before the treatment program begins. The primary outcome measure will be the Percentage of Stuttered Syllables (%SS) obtained from an unscheduled telephone call. Secondary outcome measures will include Severity Rating (SR) and Speech Naturalness obtained from an unscheduled telephone call, and the Overall Assessment of the Speaker's Experience of Stuttering (OASES). After completing these assessments, each participant will engage in treatment sessions. Post-treatment assessments will be conducted immediately after, 6 weeks after, and 3 months after the treatment to evaluate changes in primary and secondary outcome measures and to assess the maintenance and long-term stability of the results.

The study will focus on adults with moderate-to-severe stuttering. Therefore, stuttering severity will be evaluated before recruitment to confirm enrollment eligibility. The severity of stuttering will be assessed by calculating SS% in unscheduled telephone call for each participant. At the baseline assessment, a 10-min unscheduled telephone call with each participant will be conducted by individuals other than the researcher and this call will be recorded using a call recorder application. Using these data, the primary outcome measure (SS%) will be calculated. Two experienced specialist raters will independently evaluate and calculate the SS% of all speech samples. To assess interrater reliability, Cohen's kappa will be calculated. If the raters agree (intraclass correlation coefficient between 0.8 and 1), the SS% will be reported. However, if there is disagreement (intraclass correlation coefficient below 0.8), a third senior rater will review and evaluate the SS%. The completion of the OASES questionnaire by participants constitutes the final step of the pre-treatment assessments. Following the baseline assessments, the speech therapy sessions will begin. Three time points after the final intervention session (i.e., immediately, six weeks, and three months), each participant will complete post-treatment assessments, which will be identical to the pre-treatment assessments and conducted by the same raters. The trial's design and timeline are depicted in Fig. 1.

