#### Transcranial current direct stimulation Intervention(Practice stage)

2.3.2

In this stage of treatment, participants will be randomly allocated to two groups: the intervention group (anodal tDCS) and the control group (sham tDCS). Clients will practice fluency shaping techniques as an online treatment alongside each of ten 20-min tDCS stimulations. Clients will start by reading simple sentences and monologues during the first tDCS session but will eventually progress to more challenging tasks, such as conversing with the clinician, a stranger at the clinic, making telephone calls, and performing dual tasks. The tasks will become hierarchically more complex linguistically and cognitively.

In the tDCS protocol, electrical stimulation will be administered by applying a 2 mA current through two electrodes measuring 5 cm × 7 cm. The process will last for 40 min, with 15-s ramp-up and ramp-down intervals. Each therapy session will last 60 min (20 min of stimulation, 20 min of rest, followed by another 20 min of stimulation). Accordingly, each participant will receive 10 stimulation sessions over 5 therapy sessions conducted on 5 consecutive days. The tDCS will be administered using a Starstim DC stimulator. The tDCS electrodes will consist of conductive rubber encased in sponge pockets, with saline solution used as the electrolyte-based contact medium. It will be essential to saturate the sponges thoroughly with saline. The sponges will need to be properly moistened on all sides without becoming excessively saturated to avoid any dripping. Before placing the electrodes on the scalp, the clinician will examine the skin for any damage or lesions. The same stimulation intensity parameters will be applied for both anodal and sham modes. However, in the sham mode, the device will automatically reduce the intensity after 30 s. An electroencephalogram (EEG) cap will be utilized to determine the stimulation site. The anode electrode will be positioned over the left frontal gyrus (FC5, based on the 10–20 international system) [41], while the cathode electrode will be placed over the right frontopolar region (FP2, according to the same system) [41]. Elastic rubber straps will be used to secure the electrodes in place and prevent any movement.

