#### Primary outcome measures

2.4.1

In this research, the average scores of the percentage of Stuttered Syllables (%SS) obtained from a 10-min unscheduled telephone call will serve as the primary outcome measure. A baseline assessment will be collected one week before the intervention. The identical assessment will be conducted immediately after, and six weeks and three months following the last intervention session (post-treatment assessments). A 10-min unscheduled telephone call with each participant will be conducted by individuals other than the researcher, and this call will be recorded using a call recorder application. Two experienced specialist raters, blinded to the treatment conditions and assessment time points, will independently evaluate and calculate the %SS of all speech samples. The recordings will be coded and screened to ensure anonymity. To calculate the %SS, the total number of syllables associated with unambiguous stuttering for each recorded sample will be counted, divided by the total number of syllables for that sample, and then multiplied by 100 [42]. Stuttering will be characterized as occurrences that involve either (i) repetitions of phonemes, words, or phrases, (ii) prolonged phonemes, or (iii) blocks. It will be important to highlight that, per Riley's definition of stuttering (1994), interjections, silent blocks, and repetitions of whole words or phrases will be considered stuttering if they are articulated abnormally and with tension. Otherwise, they will not meet the criteria for stuttering [43]. The expected mean %SS score at the three post-intervention time points in the anodal tDCS group will be hypothesized to be significantly lower than that found in the sham tDCS group (a diminished %SS score will indicate a less severe form of stuttering). Additionally, no significant difference will be expected between groups at the baseline time point.

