### Randomization

2.5

This study is a randomized, double-blind, sham-controlled trial, where participants will be randomly assigned to either the intervention group or the control group. The random allocation of participants will help prevent selection bias and ensure a balanced distribution of confounding factors between the study groups. For the randomization process, blocked randomization will be employed. Specifically, one of the six blocks used in this study (ABAB, BABA, AABB, BBAA, BAAB, ABBA) will be randomly selected. A will represent the intervention group, and B will represent the control group. Each participant will be assigned an ID number and allocated to one of the treatment groups. The individual who generates the random allocation will not be involved in any other phase of the trial.

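### Severity is assessed before allocation but used neither in the randomisation nor in the model, so the claim that randomisation will ensure balance is too strong for 62 participants

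*Protocol article*

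**What the plan says.** **When severity is known.** Study design (2.1) states that "stuttering severity will be evaluated before recruitment to confirm enrollment eligibility" and that "The severity of stuttering will be assessed by calculating SS% in unscheduled telephone call for each participant". This is the same kind of measurement as the primary outcome. Section 2.4.1 adds that "A baseline assessment will be collected one week before the intervention". Section 2.1 places the speech therapy sessions after the baseline assessments.

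**When allocation happens.** Section 2.3.2 says of the practice stage: "In this stage of treatment, participants will be randomly allocated to two groups". Both groups will by then have completed the establishment stage (2.3.1).

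**How allocation is done.** Section 2.5 says that "one of the six blocks used in this study (ABAB, BABA, AABB, BBAA, BAAB, ABBA) will be randomly selected". It names no stratification factor. The same section says that random allocation will "ensure a balanced distribution of confounding factors between the study groups".

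**What is expected at baseline.** Section 2.4.1 says that "no significant difference will be expected between groups at the baseline time point".

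**How the data are analysed.** Section 2.10 plans mixed-model ANOVAs with group between subjects and time within subjects. Baseline is one of the four time levels. No severity factor or baseline covariate is named.

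**The concern.** A severity value on the outcome scale is in hand when the envelope is opened, but nothing in the allocation uses it. Blocks of 4 control the number per arm and nothing else. Nothing later compensates, because the 2.10 model has neither a severity term nor a baseline covariate.

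The group × time interaction compares changes from baseline. If one arm happens to start with more severe speakers, that arm is expected to fall further by regression to the mean, and the difference is added to or subtracted from the apparent tDCS effect. The comparisons of mean %SS at the three post-treatment points, hypothesised in 2.4.1, are exposed in the opposite direction. At stake are precision and the credibility of a trial of 62, not its validity.

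**Working it through.** **Inputs from the protocol article.** 31 per arm, 62 in total (2.9); the six blocks of 4 (2.5); group and time as the only factors (2.10).

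**Assumed, because the article does not give them.** The distribution of %SS, the baseline–post correlation rho (0.3 to 0.6), and a severity cut near the median.

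**The plan's own figure.** The 62 comes from an effect size of 0.17, alpha 0.05 and power 0.80. With the usual noncentrality f²·N·m·ε/(1 − rho) and m = 4, rho = 0.5 and ε = 1 give N = 50, while rho = 0.5 and ε = 0.7 give N = 62. Since rho and ε are not stated, 62 is attainable but cannot be verified. The point here uses 62 only as given.

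**Size of the chance gap, unstratified.** In units of the baseline SD, SE = √(2/31) = 0.254, so the 95% range is ±1.96 × 0.254 = ±0.50 SD.
- P(gap > 0.25 SD) = 2[1 − Φ(0.25/0.254)] = 0.32
- P(gap > 0.30 SD) = 0.24
- P(gap > 0.50 SD) = 0.05

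**With two strata.** A median split of a normal variable leaves within-stratum variance 1 − 2/π = 0.363. The SE becomes about 0.254 × √0.363 = 0.153. Simulation with the six listed blocks gives 0.156, slightly more because of unfinished blocks.

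| | One list | Two strata, normal | Two strata, lognormal (log-SD 0.6) |
|---|---|---|---|
| SD of the gap | 0.254 | 0.156 | 0.187 |
| Gap > 0.25 SD | 32% | 11% | 17% |
| Gap > 0.5 SD | about 5% | 0.1–0.2% | about 1% |

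With a median split, the arms differ by 5 or more higher-severity participants in 26% of unstratified trials and in none of the stratified ones. If only 30% fall in the upper stratum, a gap over 0.3 SD falls from 24.3% to 7.6%.

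**How the gap reaches the effect estimate.** With equal SDs at baseline and post-treatment, a baseline gap d shifts the change contrast by (1 − rho)d and the raw post-treatment contrast by rho·d. At rho = 0.5, a gap of 0.25 SD shifts either by 0.125 SD, and a gap of 0.5 SD by 0.25 SD.

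**What each remedy gains.** Variance per participant of the baseline-to-post contrast:
- Plain change score: 2(1 − rho).
- Change with stratum in the model: (1 − rho)²(1 − 2/π) + (1 − rho²). Relative to plain change this is [0.363(1 − rho) + 1 + rho]/2.
- Post-treatment value with baseline %SS as covariate: 1 − rho². Relative to plain change this is (1 + rho)/2.

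| rho | Stratum in model | Baseline %SS covariate |
|---|---|---|
| 0.3 | 0.777 | 0.65 |
| 0.5 | 0.841 | 0.75 |
| 0.6 | 0.873 | 0.80 |

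Simulation with allocation left unstratified gives 0.78 / 0.85 / 0.89 for the stratum and 0.66 / 0.76 / 0.82 for the covariate. Once the stratum is in the model, stratifying the allocation as well adds only about 0 to 2 percentage points.

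**Arm sizes.** 62 leaves remainder 2 on division by 4. Two strata summing to 62 can therefore leave remainders (0,2), (1,1) or (3,3). A remainder of 1 or 3 costs one participant of balance and a remainder of 2 costs at most two, so the largest gap is 2, that is 32:30. The present single list can also end 32:30.

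**The case against.** The strongest reply is that this is an option not taken rather than an error. Unstratified permuted blocks are a standard design. They balance baseline %SS in expectation, and the usual error term already allows for chance imbalance. That stands.

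A reader might go further and infer that the scheme contradicts the expectation in 2.4.1 of no significant baseline difference. It does not: a baseline test at the 5% level is non-significant in about 95% of trials under the present scheme. A reader might also infer that the results would be biased or the test invalid. The documents do not support that either: over repeated randomisation the gap averages zero and type I error is held.

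A second reply is that the precision gain belongs to the analysis. This also largely stands: a baseline covariate with allocation left as it is does better than the stratum does. Stratifying without any model term does lower the true variance (0.79 / 0.84 / 0.87 at the three correlations), but the unadjusted ANOVA's error term would not reflect it.

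Third, the article gives only one severity class, moderate-to-severe, with no numeric cut, and does not say how strongly baseline predicts outcome. All participants are expected to reach a severity rating below 2 in clinic tasks before the practice stage (2.3.1), so the correlation is unknown. The figures above are therefore conditional.

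Fourth, the outcome raters are blinded to assessment time point (2.4.1). Having them score baseline calls before allocation could reveal it. The choice of severity source has to respect this.

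What survives is that the balance claimed in 2.5 is not ensured, and that information already collected is used in neither the allocation nor the model.

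**Conclusion.** The point holds as one of precision, visible balance and wording. The randomisation is valid. The claim in 2.5 is too strong, because with 31 per arm a baseline %SS gap above 0.25 SD is expected in about one trial in three and a gap above 0.5 SD in about one in twenty. The 2.10 model passes (1 − rho) of any such gap into the change contrast.

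Most of the recoverable precision comes from a model term: variance falls by about 13–22% with a severity stratum and about 20–35% with baseline %SS, for rho between 0.6 and 0.3. Stratified allocation mainly adds visible balance. The unstratified gap probabilities rest on 31 per arm and an approximately normal difference in means. The stratified figures also assume a near-median split on a severity value close to the baseline %SS, and the variance figures assume rho and equal SDs over time.

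**What to change.** 1. **Allocation (2.5), only if it has not begun.** Prepare two envelope sets, lower and higher severity, each with its own random block sequence. Fix the cut-off in advance and apply it to the pre-recruitment severity assessment rather than to the blinded raters' baseline scores. If that assessment differs from the two-rater baseline %SS, the gain in balance will be smaller than shown.
2. **Model (2.10), in any case.** Add a term that acts on change. A stratum main effect alone shifts all four time points equally and cancels out of the baseline-to-post contrast. Use stratum × time if baseline stays a time level or, better, model the three post-treatment values with baseline %SS as a covariate.
3. **Wording (2.5).** Say that randomisation balances confounders on average, not that it ensures balance.
4. **If enrolment has begun.** Keep the allocation scheme and make only changes 2 and 3.

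**Cost.** A second list and envelope set, one model term, and no new data. A 32:30 split is possible, as it already is. Moving baseline from time level to covariate changes the primary test from the four-level interaction on which 2.9 is based, so that paragraph should be reworded to match. The number of participants need not change.
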